### Participants and recruitment

We will recruit children aged 8 to 12 years through community networks and Facebook advertising. We will aim to recruit a sample of children that is broadly representative of New Zealand children to increase the generalisability of findings (e.g. 50% female, 30% overweight/obese, 60% European, 21% Māori, 11% Pacific, 11% Asian). Interested families will complete an online questionnaire assessing their child’s eligibility as follows: 8–12 years of age; reported time in bed of 8–11 h per night; no underlying medical condition (e.g. healthy children); and a score of 39 or less on the Sleep Disturbance Scale for Children [58]. Participants will be excluded outside of this age group, if they have a medical condition or take medication that affects sleep or eating behaviour, or sleep disturbances are indicated. Only children with reported time in bed (time between lights out and waking in the morning) of 8–11 h a night will be eligible to ensure that any sleep extension or restriction does not place them in the “not recommended” category for sleep duration according to international guidelines (< 7 or > 12 h) [59]. There should be little concern over potential safety aspects as our eligibility criteria ensure that children should not go below the minimum recommended sleep duration. Further support for this conclusion is provided by studies showing that any effect of sleep restriction on cognition, specifically vigilance, in children is surprisingly small [60],with no long-lasting effects on cognition because recovery from restricted sleep occurs quickly; thus the one week between intervention exposures is considered sufficient to eliminate effects of prior sleep deprivation [23, 66].

Primary caregivers (parents or legal guardians) of potentially eligible participants will access the screening questionnaire, the Sleep Disturbance Scale for Children (SDSC) [58], via the University of Otago Child and Teen Sleep Research Group on Facebook (see Table 1 for the timing of all study assessments). The well-validated SDSC will identify for exclusion those children who have potential sleep problems such as sleep-walking, restless legs, sleep disordered breathing, problems with initiating and maintaining sleep, and excessive sleepiness (score of ≤39 will be eligible). Total SDSC scores will be reviewed by a Paediatric Sleep Physician to make the final determination in regard to eligibility. Caregivers of eligible applicants will be contacted by a researcher to schedule study appointments. Caregivers of applicants who are deemed ineligible due to their SDSC score will be contacted via text or email with feedback from the Paediatric Sleep Physician review as to why their child was not considered eligible. This feedback will include advice on whether they should consult their Primary Care Physician in regard to their child’s sleep health. Upon completion of the study, participants will receive a $100 voucher, and their primary caregiver will receive a $50 voucher. Participants can withdraw from the study at any time.

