**Methods:**

The Daily, Rest, Eating, and Activity Monitoring (DREAM) study is a randomized controlled trial investigating how mild sleep deprivation influences eating behaviour and activity patterns in children using a counterbalanced, cross-over design. One hundred and ten children aged 8–12 years, with normal reported sleep duration of 8–11 h per night will undergo 2 weeks of sleep manipulation; seven nights of sleep restriction by going to bed 1 hr later than usual, and seven nights of sleep extension going to bed 1 hr earlier than usual, separated by a washout week. During each experimental week, 24-h movement behaviours (sleep, physical activity, sedentary behaviour) will be measured via actigraphy; dietary intake and context of eating by multiple 24-h recalls and wearable camera images; and eating behaviours via objective and subjective methods. At the end of each experimental week a feeding experiment will determine energy intake from eating in the absence of hunger. Differences between sleep conditions will be determined to estimate the effects of reducing sleep duration by 1–2 h per night.

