**Fig. 1 Fig1:**
[figure not shown]
Study design

Benefits of the cross-over design include a reduction in the influence of confounders as each child acts as their own control. The week between weeks 3 and 5 with no intervention should eliminate any carry-over effects from one condition to the other [53]. Period effects (that their first visit is different to their second, regardless of condition due to learning effects, or comfort levels at the study, etc.) will be accounted for by randomising to order and including this in the model. The difference between these two conditions should produce a reduction in “usual” sleep time of 1–2 h per night for each child, considered to be a level of mild sleep deprivation common in children [54]. Others report high compliance (95% retention) with similar protocols in children [55, 56],

We have chosen to use a combination of sleep restriction and extension (1 hour each for seven consecutive nights) rather than comparing 2 h of restriction against usual sleep (e.g. baseline against a week of restriction) as pilot work indicated this was more feasible and practical for families. As this is a cross-over trial and children are only compared with themselves, controlling for season is not necessary; however, to remove the potential modifying effect of school holidays, all data collection will be conducted during the school term. In this way, changing bed time while maintaining wake time reflects the real world where wake times remain relatively constant in children [57]. Participants will also undergo two 24-h diet recall sessions during each experimental week. As participants will commence the study on different days of the week, all days of the week will be represented. Wearable cameras will aid researchers in validating the diet recalls. At the end of each experimental week, participants will visit the clinic for a feeding study to assess eating in the absence of hunger. Finally, families will be invited to attend a qualitative exit interview after the study ends, by a researcher with mixed methods experience that has had no previous contact with the participant or caregiver. This qualitative interview will be open-ended and serve as an explanatory tool to compliment the study. All interviews will be audio recorded and professionally transcribed, and analysed thematically. Tables 1 and 2 describe DREAM study events and event locations.

**Table 1 Tab1:** Timing of DREAM activities and study periods

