### Baseline and randomisation

Eligible participants will be seen at a 45–60 min baseline appointment in their home (week 1, Table 1). Primary caregivers will provide written consent for minors at this time, as well as complete online questionnaires assessing demographics (child date of birth, date of survey, household address to calculate household deprivation, ethnicity, family structure), child food preferences and allergies (to plan for the feeding experiment in weeks 3 and 5), and the Children’s Sleep Hygiene Survey [63]. Consent will also be gained from each child participant. Height (Wedderburn Portable Height Rod, WS-HRP) and weight (Tanita electronic scales HD351) will be measured following standard procedures, and an actigraph (the ActiGraph wGT3X-BT) will be provided to be worn on the child’s right hip 24-h a day for 1 week to measure usual sleep, physical activity and sedentary behaviour, initialized with 15 s epochs.

Families will be provided with a Participant Instruction Booklet containing all study instructions. After the baseline appointment is complete, participants will be randomised to start with either sleep restriction or sleep extension during intervention weeks 3 and 5. Randomisation will be stratified by age (grouped by 8–10 and 11–12 years) and gender. Randomisation to order will be generated using random block lengths (Stata 15.1, StataCorp, Texas) and uploaded into the REDCap randomisation module [67].

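### With reported time in bed as the criterion, a child admitted at 8 h has 7.0 h in bed under restriction, so the criteria cannot assure the 7 h sleep minimum

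*Protocol article*

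**What the plan says.** All places are in the protocol article.

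- Participants and recruitment: the quantity that must lie between 8 and 11 h is "reported time in bed (time between lights out and waking in the morning"). Its purpose is to keep children out of the not-recommended "category for sleep duration according to international guidelines (< 7 or > 12 h"). The section concludes that "our eligibility criteria ensure that children should not go below the minimum recommended sleep duration". As a second ground for reassurance it cites studies in which "any effect of sleep restriction on cognition, specifically vigilance, in children is surprisingly small", with quick recovery and nothing long-lasting.
- Same section, on screening: the Sleep Disturbance Scale for Children is used to exclude, among others, children with "problems with initiating and maintaining sleep", and a paediatric sleep physician decides final eligibility.
- Abstract, Methods: the same range is described as children "with normal reported sleep duration of 8–11 h per night".
- Intervention: bed time is moved by 1 h for seven nights, the usual wake time is kept, and naps are not allowed. Usual times come from questionnaire, diary and week-1 actigraphy, separately for weekdays and weekends.
- Study design and setting: the two conditions together should differ in "sleep time of 1–2 h per night for each child".
- Baseline and randomisation: "After the baseline appointment is complete, participants will be randomised to start with either sleep restriction or sleep extension".

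**The concern.** The criterion and the limit are on different scales. The criterion is the interval from lights out to waking, as a caregiver reports it. The limit is on sleep. The interval contains the time taken to fall asleep and any waking in the night, so it can only be longer than sleep or equal to it. The abstract's label for the same range suggests that the two were treated as one quantity.

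Elsewhere the article keeps them apart. Measurement of sleep and activity estimates sleep onset, sleep offset and wake after sleep onset. Feasibility and pilot work reports the difference in time in bed and the reduction in sleep as separate results.

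At stake is the first of two reasons given for little safety concern when children's sleep is deliberately shortened. An ethics committee, or a team copying the design, could rely on it.

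**Working it through.** **Inputs from the article.** Reported time in bed 8 to 11 h; limits 7 h and 12 h of sleep (Participants and recruitment). Delay or advance of 1 h, wake time fixed, no naps (Intervention). Sleep cut by almost one hour per night in the pilot's restriction week (Feasibility and pilot work).

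**Inputs not in the article, assumed here.** Time awake in bed, L: 15 or 30 min, taken as unchanged by the later bed time. Alternatively, sleep efficiency, e: 95, 90 or 85%. A value of 0.9 h as one reading of the pilot's almost one hour.

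**The plan's own limits.** Lower: 8 − 1 = 7.0 h. Upper: 11 + 1 = 12.0 h. Both reproduce exactly, but as time in bed. They are limits on sleep only if no minute in bed is spent awake.

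**Lower limit, sleep.** Sleep = 8 − L − r, with r the sleep lost to the later bed time.

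| r | L = 0.25 h | L = 0.5 h |
|---|---|---|
| 1.0 h | 6.75 h (15 min under) | 6.50 h (30 min under) |
| 0.9 h | 6.85 h (9 min under) | 6.60 h (24 min under) |

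Sleep is under 7 h when L > 1 − r. At r = 1.0 h any time awake is enough; at r = 0.9 h it takes more than 0.1 h, or 6 min.

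**How far up the range this reaches.** With r = 1.0 h, usual time in bed must be at least 7 + 1 + L, which is 8.25 or 8.50 h. By efficiency it must be at least 7/e + 1, which is 8.37, 8.78 or 9.24 h for e = 95, 90 or 85%. With 7.0 h in bed, those efficiencies give 6.65, 6.30 or 5.95 h of sleep. These are points on the time-in-bed scale. The article does not give the share of children below them.

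**Upper limit, sleep.** 12.0 h in bed gives at most 12 h of sleep (11.75 or 11.5 h with the assumed L). This limit holds.

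**A cap on the delay.** Let S be usual measured sleep. Delay = max(0, min(1, S − 7)) h, and nominal contrast = 1 h of extension + delay.

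| S | Delay | Nominal contrast |
|---|---|---|
| 8 h or more | 1 h | 2 h |
| 7.75 h | 0.75 h | 1.75 h |
| 7.5 h | 0.5 h | 1.5 h |
| 7 h or less | 0 | 1 h |

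The lower bound of zero is needed. Without it, S = 6.8 h (8 h in bed at an assumed 85% efficiency) gives 6.8 − 7 = −0.2 h, a bed time 12 min earlier than usual in the restriction week and a contrast of 0.8 h.

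If an assumed 5, 10 or 20% of children had their delay cut by 30 min, the mean contrast would fall by 0.05, 0.10 or 0.20 × 30 = 1.5, 3 or 6 min. That is a favourable case. At 85% efficiency, S is below 8 h for everyone with usual time in bed under 8/0.85 = 9.4 h, and the average loss would be larger.

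**The case against.** The best defence is that the guideline's 7 h may itself refer to sleep as caregivers report it, which is close to lights out to waking. The criterion would then fit the limits exactly at both ends, and 7.0 h is not below 7 h. The exact match suggests that the authors worked on that scale. The guideline is not available here, so this cannot be excluded. It still leaves the child on the limit with nothing to spare, while the article names the limit as one on sleep duration.

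The wording is also softened: children should not go below the minimum. That hedge counts for something, but the section speaks of ensuring twice. Screening for sleep disturbance and the physician's decision make long periods awake less likely; they do not create a margin for a healthy child who takes a few minutes to fall asleep. Bed times are tailored to each child and checked with caregivers, but the text attaches no floor to that step.

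A reader might infer that the trial has no floor at all. An article condenses a fuller protocol, and a floor may be set there. If so, that rule would protect the child, and the printed credit to the eligibility criteria would still be misplaced.

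A reader might also infer that a known group of children will sleep 15 to 30 min too little. That is not supported: every shortfall above rests on an assumed waking time, and nothing shows how many children near 8 h will enrol.

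**Conclusion.** The statement that the eligibility criteria secure the 7 h minimum is not supported. What is certain is the arithmetic: 7.0 h in bed for a child admitted at 8 h, with no margin for time awake. The size of any shortfall depends on assumed waking times, and whether the guideline limit is crossed or only touched depends on the scale the guideline uses.

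The point concerns the lower end of the eligible range, for up to seven nights. It should not be read as showing that the design is unsafe: the second ground, that effects are small and quickly reversed, does not rest on the criterion and is unaffected. The 12 h limit, the power calculation and the primary analysis as planned are also unaffected. Severity: minor.

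**What to change.** When personal bed times are set from the week-1 actigraphy and diary, limit the restriction-week delay to max(0, min(1 h, usual measured sleep − 7 h)). Keep children with a shortened or zero delay in the analysis as randomised. Because randomisation as worded follows the baseline appointment, at which the actigraph is handed out, measured sleep is not yet known at that point. A rule on the bed time therefore fits the schedule better than a further exclusion. For a child whose usual sleep is already under 7 h, the rule only avoids adding to the deficit.

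The cost is one rule, with no new measurement and no change to eligibility or randomisation. It gives up the uniform dose. The contrast in capped children shrinks and can fall to about 1 h, the bottom of the intended 1–2 h, where usual measured sleep is near or below 7 h. The average loss exceeds the 1.5 to 6 min illustrated if many children usually sleep under 8 h. The week-1 data would show how many.

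If the sponsor prefers a uniform 1 h delay, withdraw the assurance, say that children near 8 h in bed may sleep under 7 h for up to seven nights, and rest the safety case on the short exposure and the cited evidence of small, quickly reversed effects. That costs a short rewording.

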### Study administration

Study data will be collected and managed using Research Electronic Data Capture (REDCap) tools hosted at the University of Otago [67]. REDCap is a secure, web-based application designed to support data capture for research studies, providing an intuitive interface for validated data entry, audit trails for tracking data manipulation and export procedures, automated export procedures for seamless data downloads to common statistical packages, and procedures for importing data from external sources. Practically speaking, REDCap allows for the tracking of participants, the dissemination of surveys, the managing of appointments, online questionnaire entry, and all other data entry in one place.

### Baseline and randomisation

Eligible participants will be seen at a 45–60 min baseline appointment in their home (week 1, Table 1). Primary caregivers will provide written consent for minors at this time, as well as complete online questionnaires assessing demographics (child date of birth, date of survey, household address to calculate household deprivation, ethnicity, family structure), child food preferences and allergies (to plan for the feeding experiment in weeks 3 and 5), and the Children’s Sleep Hygiene Survey [63]. Consent will also be gained from each child participant. Height (Wedderburn Portable Height Rod, WS-HRP) and weight (Tanita electronic scales HD351) will be measured following standard procedures, and an actigraph (the ActiGraph wGT3X-BT) will be provided to be worn on the child’s right hip 24-h a day for 1 week to measure usual sleep, physical activity and sedentary behaviour, initialized with 15 s epochs.

Families will be provided with a Participant Instruction Booklet containing all study instructions. After the baseline appointment is complete, participants will be randomised to start with either sleep restriction or sleep extension during intervention weeks 3 and 5. Randomisation will be stratified by age (grouped by 8–10 and 11–12 years) and gender. Randomisation to order will be generated using random block lengths (Stata 15.1, StataCorp, Texas) and uploaded into the REDCap randomisation module [67].

### Intervention

Data from three sources (questionnaire detailing usual sleep times, sleep diary records, and actigraphy) will be triangulated to determine usual sleep onset and offset for each child, separately for weekdays and weekends. The actigraphy results will be used to guide personalised intervention during experimental weeks 3 and 5 (e.g. double checking with caregivers that data gathered reflected usual behaviour). Based on their randomisation group, each child will be instructed to go to bed 1 hr later or earlier than their usual bed time each night for seven nights, while maintaining the usual wake up time determined during baseline week 1. Following a week of no intervention (week 4) the child will then undergo the opposite intervention in week 5.

Naps will not be permitted during the study. Field researchers will work with families and children to determine how best to ensure adherence for each family using strategies such as pre-planning, problem solving and positive reinforcement, based on their individual screening results [68]. During the two sleep intervention weeks, daily bed time text reminders will be sent to either the primary caregiver, the child, or both, depending on individual request, to encourage adherence. Text reminders will also be sent to remind participants when to wear the cameras, as described below. These reminders will be sent by an online platform or wireless software application. Upon completion of the project, all child participants will receive a $100 voucher, and primary caregivers a $50 voucher, to reimburse them for their time.

### Measurement of sleep and activity

We will use the same procedures as during baseline (full week of 24-h measurement). ActiLife software (version 9.0.0) will be used to initialise and download the actigraphy data, and an automated script developed in MATLAB® (MathWorks, Natick, MA, USA) will be used for analysis of sleep and activity patterns. The automated MATLAB® script uses a count-scaled algorithm to estimate sleep onset and offset for overnight sleep and awakenings (wake after sleep onset, WASO) [69] specific to each individual for each day [70]. Once these sleep data are effectively “removed” from the 24-h day, time spent sedentary and at various intensities of activity can be determined. Non-wear time will be defined as at least 20 min of consecutive zeros during awake time data [71]. The cut-offs of Evenson et al [72] will be used to denote time in sedentary, light, moderate and vigorous activity as recommended by Trost et al [73] for our age range. Appropriate statistical techniques will be used to determine whether the loss in sleep time decreased time spent being active or increases the proportion of time spent sedentary [48, 63].

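### The non-wear rule covers awake time only, so a hip monitor taken off in the evening or overnight can be counted as sleep without being detected

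*Protocol article*

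**What the plan says.** Under Baseline and randomisation, the monitor is to be "worn on the child’s right hip 24-h a day for 1 week to measure usual sleep, physical activity and sedentary behaviour". Under Measurement of sleep and activity, the experimental weeks follow suit: "We will use the same procedures as during baseline (full week of 24-h measurement".

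That section then fixes a sequence:

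1. An automated script "uses a count-scaled algorithm to estimate sleep onset and offset for overnight sleep and awakenings (wake after sleep onset, WASO").
2. "Once these sleep data are effectively “removed” from the 24-h day, time spent sedentary and at various intensities of activity can be determined".
3. "Non-wear time will be defined as at least 20 min of consecutive zeros during awake time data".

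Under Intervention, a second source is named for the baseline week: "Data from three sources (questionnaire detailing usual sleep times, sleep diary records, and actigraphy) will be triangulated to determine usual sleep onset and offset". Caregivers are also consulted ("double checking with caregivers that data gathered reflected usual behaviour"). The purpose there is to set each child's usual times, from which the bed-time instruction follows. The same section moves bed time by 1 h in either direction and holds wake time.

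**The concern.** A still, unworn monitor records zero counts, and a sleeping child largely does too. A count-based algorithm has little to tell them apart, and the one non-wear rule in the article is confined to time the algorithm has already called awake. An unworn stretch that the algorithm takes for sleep therefore lies outside the rule.

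The place where this can happen matters. Wake time is held and bed time is moved, so the whole manipulation lies in the evening. A monitor taken off before bed produces zeros that run straight into true sleep, and the error falls on the interval by which the two conditions differ.

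Two uses of the data are exposed. One is the check that the intended difference of 1–2 h per night was achieved. The other is secondary aim 6. The Background stresses that the 24-h day is closed, so minutes wrongly given to sleep are taken from sedentary or active time, which is the trade-off the trial wants to estimate.

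**Working it through.** **Does the written rule reach non-wear inside scored sleep?** No. Sleep is identified first, that time is removed, and the 20-min zero rule is applied to awake data. No other non-wear rule is stated. The diary appears under Intervention (to set usual times at baseline) and under Feasibility and pilot work (pilot adherence). In neither place is it tied to scored sleep in weeks 3 and 5, and Table 1 lists actigraphy but no sleep diary.

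**Is a published figure affected?** No figure in the article depends on this rule. The main sample size needs no actigraphy input: SD of the difference = 870 × √(2 × (1 − 0.7)) = 673.9 kJ, and a paired t calculation for 250 kJ at 80% power and two-sided 5% gives the stated 59.

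**How large could the effect be?** The documents give no wear rates, so this is an illustration.

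Inputs:
- True sleep contrast C = 1.5 h. This is an assumption. The pilot's 1.5 h is a difference in time in bed, not in sleep, so C = 1.0 and 2.0 h (the planned range) are shown as well.
- Share of nights affected f = 1/14, 1/7 or 2/7 (assumed).
- Unworn pre-bed time is scored as sleep (assumed; the article does not say).

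Patterns and formulas:
- (a) Removed at the same clock time in both weeks, before the earlier bed time. Scored sleep is then equal on those nights, so the measured contrast = (1 − f) × C.
- (b) Removed the same interval before bed in both weeks: measured contrast = C.
- (c) Removed in the restriction week only, 1 h before bed: C − f × 1 h.
- (d) Removed in the extension week only, 1 h before bed: C + f × 1 h.

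Measured contrast in hours for C = 1.5:

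| Pattern | f = 1/14 | f = 1/7 | f = 2/7 |
|---|---|---|---|
| (a) same clock time | 1.39 | 1.29 | 1.07 |
| (b) same interval before bed | 1.50 | 1.50 | 1.50 |
| (c) restriction week only | 1.43 | 1.36 | 1.21 |
| (d) extension week only | 1.57 | 1.64 | 1.79 |

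For example, (a) at f = 2/7 is (5/7) × 1.5 = 1.07 h, and (d) at f = 2/7 is 1.5 + 2/7 = 1.79 h. Over the same patterns, C = 1.0 h gives 0.71 to 1.29 h and C = 2.0 h gives 1.43 to 2.29 h.

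The contrast can shrink, stay the same or grow.

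**The case against.** The strongest reply is that the article does not describe how the algorithm treats long runs of zeros, whether it limits the window for sleep onset, or whether it uses diary times. Those details sit in cited sources or a scoring manual, and an article may leave valid-night criteria to the full protocol. This stands against any statement that unworn time is scored as sleep. It does not remove the point, because the limit to awake time is written in the article.

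A reader might infer more: that the monitor will come off at the usual hour in the restriction week, so that the restriction seems not to have happened. The documents do not support that. They ask for 24-h wear and give no removal pattern. Removal at a constant interval before bed cancels within the child, and removal in the extension week only would inflate the contrast. A monitor left off from true bed time onward need not alter the scored sleep onset. The pilot, from actigraphy and diaries, reports sleep cut by almost one hour per night in the restriction week. That is mild reassurance only, since it covers 11 children and gives no wear rate.

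It can also be said that diaries already offer a cross-check. They do as a source, but their stated use is to set usual times at baseline. Finally, limiting the 20-min rule to awake data has a good reason: a motionless sleeping child can also yield long zero runs, so running the rule over the whole record could delete genuine sleep. That stands and shapes the fix.

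**Conclusion.** The point holds as a gap in a stated rule. Non-wear in the evening or overnight can be scored as sleep, and nothing in the article would detect it. Measured sleep, the achieved contrast and the 24-h composition for secondary aim 6 can be biased, in a direction that depends on wear patterns the documents do not give. Under the illustrative assumptions with a true contrast of 1.5 h, the measured value lies between 1.07 and 1.79 h, with no distortion in the symmetric case. These figures assume that the algorithm takes unworn zeros for sleep.

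It should not be read as a threat to the main result. The primary comparison of energy intake in the absence of hunger is by assigned sleep condition, rests on weighed food, and uses no actigraphy. Its sample size is likewise unaffected.

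**What to change.** - Keep the 20-min zero rule for awake time.
- Add a night-level check in weeks 1, 3 and 5. Flag a night if its scored sleep is an essentially unbroken run of zeros, or if such a run begins before the diary bed time. Define what counts as essentially unbroken before the data are analysed.
- For flagged nights, set sleep and the overlapping 24-h composition to missing instead of counting the time as sleep.
- Do not drop nights for disagreement with the diary alone, since that could erase real non-adherence.
- State that the sleep diary is kept in both experimental weeks, and report the number of flagged nights by condition.

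The cost is a small change to the automated script and the loss of some nights to missing data. The pilot already analysed diaries alongside actigraphy, so the second source is feasible.
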